##### PIP-PCOS

In a relationship where the couple is having regular, unprotected sexual intercourse and pregnancy is desired42 years of age or younger at the time of randomisationMeet the Rotterdam criteria for PCOS, at least two of the following [37]:Oligoovulation or anovulation (confirmed by luteal phase progesterone test or history of irregular cycles)Excess androgen activity (elevated serum testosterone or clinical signs such as excess hair)Polycystic ovaries (as evidenced on ultrasound)Male partner has had a normal semen analysis in the last five years according to WHO criteria [36] (volume ≥1.5 ml, progressive motility ≥32 %, concentration ≥15 million/ml) or total motile count >10 millionHave eitherTwo ovaries and two probably patent fallopian tubes (normally confirmed by laparoscopy or HSG)A previous intrauterine pregnancy, and no subsequent surgery, infection or ectopic pregnancy that may reduce tubal patencyConfirmed to have ovulated in a total of six or fewer ovulation induction cycles (as assessment of tubal patency may not be recommended until failure to achieve pregnancy following a number of cycles of successful ovulation)Body mass index (BMI) ≤ 35 kg/m^2^Willing and able to have regular sexual intercourse in the cycle in which the procedure is performed, and for two cycles following the procedurePlanning to undergo at least three consecutive cycles of ovulation induction (unless pregnancy occurs prior to completion of three study cycles).

#### Exclusion criteria

Women who meet the following exclusion criteria are not eligible to take part in the PIP studies:

##### PIP-IVF, PIP-PCOS and PIP-UE

Have had any disruptive instrumentation within the uterine cavity (for example, hysteroscopy, hysterosalpingography, laparoscopy, surgically managed miscarriage or endometrial biopsy) within three months prior to day one of the planned embryo transfer cycle/menstrual cycle/ovulation induction cycle, or planning to undergo a procedure involving disruptive instrumentation at any stage during the study. Embryo transfer and intrauterine insemination (IUI) procedures are not considered to cause disruptive instrumentationEntered previously into this study or participated in another trial in the last 30 daysAny contraindication to endometrial biopsy and/or being pregnant and/or carrying a pregnancy to term.

##### Additional exclusion criteria for PIP-UE

4.On ovulation induction medication or any other fertility treatment or planning any fertility treatment during the study period5.Have had a miscarriage in the last 12 months or have moderate or severe endometriosis (grade 3 or 4) and therefore do not meet the criteria for unexplained infertility [38]6.Have recurrent miscarriage (spontaneous loss of three or more clinical pregnancies [39]).

##### Additional exclusion criteria for PIP-PCOS

The presence of any other cause of infertility, where spontaneous conception is unlikely (for example, large fibroids, moderate or severe endometriosis (grade 3 or 4) or severe male factor)Have recurrent miscarriage (spontaneous loss of three or more clinical pregnancies [39])

### Standard care

Standard care will be identical in both arms of each PIP study. The PIP studies are pragmatic trials, and standard care may differ slightly between participating centres. For example, some centres may prefer an antagonist protocol and others may prefer a long course agonist protocol for IVF cycles.

Participants in PIP-IVF are either taking part in an IVF/ICSI cycle involving controlled ovarian stimulation, oocyte collection and fresh embryo transfer, or are planning a frozen-thaw embryo transfer. Any IVF protocol or use of additional treatments, such as pre-implantation genetic diagnoses or assisted hatching, is acceptable. Similarly, artificial, manufactured and natural cycles for frozen-thaw embryo transfers are acceptable.

PIP-PCOS participants are on ovulation induction medication: clomiphene, letrozole, follicle-stimulating hormone (FSH) or metformin. The choice of medications, dosages and combinations of medications may vary.

Participants in PIP-UE should not be on any fertility treatment. Participants in PIP-PCOS and PIP-UE are asked not to undergo any additional fertility treatment; for example, IUI and IVF are considered protocol violations. Vitamins, dietary supplements and other medications or procedures which are not normally considered fertility treatments, such as acupuncture, are permitted in all studies.

### Eligibility assessment

Potentially eligible women will be informed about the PIP study by invitation letter, advertisement (for example, poster or newsletter) or their treating clinician or nurse. All potential participants will have the opportunity to ask questions about the study and discuss any concerns or queries prior to making a decision about whether to take part. Informed consent will be obtained from all participants in writing prior to their recruitment. Informed consent will be undertaken by a PIP study researcher who is familiar with the study details and has adequate training and experience in trial recruitment (see Tables 1 and 2).

**Table 1 Tab1:** Schedule of procedures and outcome measurements for PIP-IVF

	Pre-study	Day 1 of prior cycle	Day 3 of prior cycle-day 3 of IVF/embryo transfer cycle	Day after procedure	IVF cycle/embryo transfer	About 2 weeks after embryo transfer	About 6 weeks gestation	≥12 weeks gestation	Birth
Eligibility screen	x								
Informed consent	x								
Randomisation		x							
Endometrial scratching (intervention group only)			x						
Pain (VAS) (intervention group only)			x						
Adverse events (intervention group only)			x	x					
Bleeding (intervention group only)				x					
IVF cycle characteristics					x				
Biochemical pregnancy						x			
Clinical pregnancy							x		
Ongoing pregnancy								x	
Live birth									x

**Table 2 Tab2:** Schedule of procedures and outcome measurements for PIP-UE and PIP-PCOS

	Pre-study	Day 1-12 of cycle 1	Day after procedure day	End of study/end of cycle 3	About 6 weeks gestation	≥12 weeks gestation	Birth
Eligibility screen	x						
Informed consent	x						
Randomisation		x					
Study intervention		x					
Pain (VAS)		x					
Adverse events		x	x				
Bleeding			x				
Cycle characteristics (e.g., intercourse frequency, ovulation medication dose (PIP-PCOS only), via study diary)				x			
Clinical pregnancy					x		
Ongoing pregnancy						x	
Live birth							x

The details of all women assessed for eligibility will be recorded to ensure reporting as per the CONSORT statement [40]. This record will include reasons for ineligibility or nonparticipation.

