### Outcomes

The primary outcome is live birth rate per woman randomised, as defined previously [35].

Secondary outcomes include:ongoing pregnancy per woman randomised (defined as continuing pregnancy diagnosed by ultrasonographic visualisation of one or more gestational sacs on or after 12 weeks gestation)clinical pregnancy per women randomised (defined as a pregnancy diagnosed by ultrasonographic visualisation of one or more gestational sacs, including ectopic pregnancy)biochemical pregnancy (defined as βhcg > 25 mIU/ml) PIP-IVF onlymultiple pregnancies per women randomised and per clinical pregnancy (defined as ultrasonographic visualisation of two or more gestational sacs or heartbeats)ectopic pregnancy per women randomised and per clinical pregnancy (defined as a pregnancy in which implantation takes place outside the uterine cavity)miscarriage per women randomised and per clinical pregnancy (defined as the spontaneous loss of a clinical pregnancy before 20 completed weeks of gestational age)neonatal characteristics (for example, gender, gestation at birth, malformations)placenta characteristics (placenta previa: major, placenta previa: minor, placental abruption, placenta accreta: previous uterine surgery, placenta accreta: no previous uterine surgery)pain during the procedure (as measured by a 10 cm visual analogue scale (VAS))bleeding the day following the procedure.

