### On-study period (study duration)

#### ᅟ

##### PIP-IVF

Women in PIP-IVF who undergo embryo transfer are usually scheduled for a serum human chorionic gonadotrophin test to confirm pregnancy approximately two weeks following embryo transfer (Table 1). Women with a positive pregnancy test will be followed up to determine clinical pregnancy by ultrasound at approximately six weeks gestation. The cycle prior to embryo transfer and the embryo transfer cycle are defined as the on-study period (Fig. 2). If the participants’ IVF cycle or embryo transfer is delayed, the recorded outcome will be the pregnancy result of the first embryo transfer which takes place within three calendar months of the expected day one of the embryo transfer cycle/day one of stimulation injections. The expected day one of the embryo transfer cycle is recorded at the time of randomisation.

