### Interim analyses and data and safety monitoring

No interim analyses will be conducted. No data safety monitoring committee will be established.

Adverse events are defined as any untoward medical occurrence in a randomised patient regardless of its causal relationship to study treatment. Provision has been made for actively recording adverse events which are expected, for example, miscarriage, multiple gestations and pain during the procedure. Additionally, due to concern regarding the possible influence of endometrial disturbance on the implantation site of an embryo, the location of the placenta will be recorded following live birth.

Participants will be asked to report any other adverse events to the study coordinator when they occur; these will not be actively recorded. All adverse events that occur during the study period will be documented on a designated data form. It should be noted that endometrial biopsy is a safe and well-tolerated procedure which is routinely performed in women in whom uterine pathology is suspected, for example, women with menorrhagia. Adverse events and complications related to this procedure include infection, haemorrhage and perforation of the uterus, but these are rare [6, 7].

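### PIP-IVF: Table 1 schedules general adverse events for the biopsy arm only and to the day after the procedure, against the protocol's own definition, so no balanced comparison of non-pregnancy events is assured

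*Protocol article*

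**What the plan says.** Three places in the protocol article bear on this.

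- **Eligibility assessment, Table 1 (PIP-IVF schedule).** The row reads "Adverse events (intervention group only"). It has a mark in the procedure window and one on the day after the procedure, and none afterwards. The pain and next-day bleeding rows carry the same arm restriction.
- **Interim analyses and data and safety monitoring.** The definition is "Adverse events are defined as any untoward medical occurrence in a randomised patient regardless of its causal relationship to study treatment". The documentation rule is "All adverse events that occur during the study period will be documented on a designated data form". Neither sentence is limited by arm. Recording is then split in two. Expected events are active: "Provision has been made for actively recording adverse events which are expected, for example, miscarriage, multiple gestations and pain during the procedure". The rest are passive: "Participants will be asked to report any other adverse events to the study coordinator when they occur; these will not be actively recorded".
- **On-study period, PIP-IVF.** "The cycle prior to embryo transfer and the embryo transfer cycle are defined as the on-study period".

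The Outcomes section adds secondary outcomes with safety content and no arm restriction, among them "miscarriage per women randomised and per clinical pregnancy" and "ectopic pregnancy per women randomised and per clinical pregnancy". It also lists multiple pregnancy, neonatal characteristics and placental characteristics.

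**The concern.** A site that works from the schedule would schedule general adverse events for biopsy women on two occasions and for control women on none. A site that works from the safety section would document them in everyone for two cycles. The protocol does not say which governs.

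PIP-IVF controls have no procedure, so pain scores and next-day bleeding can only be collected in the biopsy arm. That reasoning does not carry over to events defined without regard to cause. Under Standard care both arms go through the same stimulation, oocyte collection and transfer, or a frozen-thaw transfer, so untoward events can arise in either. The trial is also open label.

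What is at stake is whether counts of infection, haemorrhage or pelvic pain from PIP-IVF can be read against a control figure. If ascertainment differs by arm, those counts can neither reassure about the biopsy nor implicate it. No interim analysis is planned and no safety monitoring committee will be set up, so the final report is where such a signal would have to be seen.

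**Working it through.** The protocol gives no figure to reproduce here. The check sets the passages side by side and then counts the women affected.

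**1. Who and when**

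| Source | Who | Period |
|---|---|---|
| Table 1 (PIP-IVF), adverse-event row | Biopsy arm only | Procedure window and day after |
| Table 2 (PIP-UE, PIP-PCOS), adverse-event row | Both arms | Same two time points |
| Safety section, definition and documentation rule | Every randomised woman | Whole study period |
| On-study period, PIP-IVF | Not limited by arm | Cycle before transfer plus transfer cycle |

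Table 1 conflicts with the safety section on both columns. Table 2 shows that the arm restriction is peculiar to PIP-IVF.

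**2. How much of the period Table 1 covers**

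The biopsy may be done no later than day 3 of the embryo transfer cycle. In a fresh cycle, day 1 is defined as the day before stimulation starts, so day 3 is the second day of stimulation. The last scheduled adverse-event mark therefore falls at latest on day 3 + 1 = day 4, the third day of stimulation. The rest of stimulation, oocyte collection and transfer lie beyond the scheduled window in both arms.

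**3. Whether other text fills the gap for controls**

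- Spontaneous reporting in the safety section has no arm restriction, but it is stated to be passive.
- The leaflet, and the advice to contact the coordinator about heavy bleeding or signs of infection (text under Placebo procedure), are given after the procedure. PIP-IVF controls have none.
- The PIP-IVF contact within one week is timed from the procedure and asks about bleeding the next day. It too has no counterpart for controls.

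Prompting is therefore tied to the biopsy, as the schedule is.

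**4. What is still compared by arm**

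Miscarriage, ectopic pregnancy and multiple pregnancy are defined per woman randomised. Placental and neonatal characteristics are listed without an arm restriction, and placental location is recorded after live birth.

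**5. Size**

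- Planned totals (end of the Sample size section): 840 + 350 + 280 = 1,470. PIP-IVF is 840 / 1,470 = 57%.
- Randomisation is 1:1, so each PIP-IVF arm has 840 / 2 = 420 women.
- General adverse events under Table 1: about 420 biopsy women scheduled, 0 of about 420 controls.
- Pregnancy outcomes per woman randomised: about 420 against 420.

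**The case against.** The best case for the plan has four parts.

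- **The row means procedure-related events.** It sits between procedure pain and next-day bleeding, and controls have no procedure. This is a plausible intention, but the row bears the general label and the protocol defines that term without regard to cause. If procedure-related events are meant, the row should say so.
- **Table 1 is not exhaustive.** It has no rows for miscarriage, ectopic pregnancy, multiple pregnancy, placental or neonatal data, all of which the Outcomes section commits to collect, so absence from the table does not prove that data go uncollected. That is right for an omission. Here, however, the table states a restriction, and it contradicts the text.
- **Controls are asked to report events, over the whole period.** This stands as far as it goes: the safety section does not exclude them. But unprompted reporting in controls is not equivalent to scheduled questions, a leaflet and a follow-up contact in the biopsy arm.
- **Infection after the biopsy is covered by the leaflet and the one-week contact.** This softens the short window for biopsy women. It also widens the difference between the arms.

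Two stronger readings are tempting, and the documents support neither. A reader might infer that PIP-IVF has no randomised adverse-event comparison at all, or that this row is its only safety information. Both are wrong, because the pregnancy, placental and neonatal outcomes are collected in both arms. A reader might also infer that events over the IVF cycle will all be counted in the biopsy arm and none in controls, producing a large spurious excess. That would need full-cycle scheduled collection in the biopsy arm, and Table 1 stops the day after the procedure. Taken literally, the table leaves later events unscheduled in both arms; the safety section, if followed, documents them in both. The size of any imbalance therefore cannot be derived from the protocol.

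**Conclusion.** The concern holds for general, non-pregnancy adverse events in PIP-IVF. Table 1 contradicts the safety section on arm and on period, and about 420 of 840 women have no scheduled collection of events such as infection, haemorrhage or pelvic pain. No balanced comparison of these events is assured. The pregnancy, placental and neonatal comparisons are unaffected, and so is the primary outcome of live birth.

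The conclusion rests on the wording of the table and the text, plus the planned total and 1:1 allocation for the count of 420. It assumes that some sites will take their data collection from the schedule. It does not depend on any assumed event rate. The point should be corrected, because the repair is cheap and the present wording leaves each site to choose.

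**What to change.** Reconcile Table 1 with the safety monitoring section:

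1. Remove the restriction to the intervention group from the adverse-event row of Table 1.
2. Ask the same short set of adverse-event questions in both arms, covering the same period counted from randomisation.
3. Use the existing contact about two weeks after transfer. That contact exists only for women who reach transfer, so define an equivalent contact at the end of the on-study period for women with no transfer. Otherwise the comparison would be confined to a group selected after randomisation, and women whose cycle was cancelled or postponed, possibly because of an adverse event, would be lost.
4. Keep the pain score and next-day bleeding for the biopsy arm only. Label these and any other events collected only around the procedure as descriptive, not comparative.

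The cost is one edited table row, one defined contact for women without a transfer, and slightly more data entry. Recruitment has begun, so the change should be dated and the report should state which women were followed under each rule.

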### Randomisation

A third-party, Internet-based, data collection and randomisation system will be used to confirm participant eligibility and ensure allocation concealment; that is, participant allocations are concealed within the system until the patient is randomised. Only participants who meet the eligibility criteria can be randomised. In instances where computer or Internet access is not reliable, participants will be randomised using sequentially numbered, opaque, sealed envelopes. Dedicated PIP study personnel will be responsible for randomising participants at each site. Participants will be randomised in a 1:1 ratio using block randomisation of two different sizes between 5–15 repeating in random order, stratified by recruiting clinic and by fresh or frozen-thaw embryo transfer (the latter in PIP-IVF only).

### Timing of randomisation and the study procedure

#### ᅟ

##### PIP-IVF

In PIP-IVF, eligible women will be randomised to the study on or after day one of the cycle that precedes the embryo transfer cycle (Table 1). For example, in participants scheduled for a long course buserelin cycle, randomisation will ideally take place on day one of the cycle, 21 days before down-regulation begins. Women will be informed of their allocation immediately after randomisation. Women randomised to the procedure group will be scheduled to undergo an endometrial biopsy procedure between day three of the cycle preceding embryo transfer and the third day of the embryo transfer cycle. Day one of the embryo transfer cycle is defined as either the day before the first day of controlled ovarian stimulation or day one of a menstrual period/withdrawal bleed for frozen-thaw embryo transfer cycles.

The large window of opportunity to perform the endometrial biopsy procedure is based on results from previous studies. Endometrial injury has been reported to have a beneficial effect as early as the menstrual period of the cycle preceding embryo transfer [20], and as late as the menstrual period following down-regulation [41]. This flexibility is also in keeping with the pragmatic nature of these studies.

##### PIP-PCOS and PIP-UE

Women who are eligible for PIP-UE or PIP-PCOS will be scheduled for the procedure between days one and 12 of a menstrual cycle (PIP-UE) or ovulation induction cycle (PIP-PCOS). The women will be randomised once they arrive at the clinic, allocating them to either undergo the endometrial biopsy or a sham procedure (Table 2).

The rationale behind timing the study procedure during the follicular phase of the cycle is threefold. Firstly, there is some concern that performing an intrauterine procedure in the luteal phase may disrupt a newly implanted embryo and therefore reduce the chance of pregnancy. Secondly, women would need to be asked to avoid conceiving during the pipelle biopsy cycle, and this would reduce the women’s overall opportunity to conceive. Lastly, it is thought that the endometrial biopsy procedure may be less uncomfortable and less likely to be abandoned due to inability to pass the pipelle if performed during the menstrual period, as the cervical canal is slightly more open. This is despite suggestion that endometrial injury induced decidulisation is more prominent in the luteal phase of the cycle [42].

The similarities and differences between the three PIP studies are outlined in Table 3.

**Table 3 Tab3:** Comparison of the design of the three PIP studies

	PIP-IVF	PIP-UE	PIP-PCOS
Standard care	IVF/ICSI/embryo transfer	No treatment	Ovulation induction medication (metformin, clomiphene,
Method of attempted conception	IVF/ICSI/embryo transfer	Intercourse	Intercourse
Randomisation timing	Approx. day 1 of cycle prior to treatment cycle	Immediately prior to the intervention	Immediately prior to the intervention
Intervention	Endometrial scratching by pipelle	Endometrial scratching by pipelle	Endometrial scratching by pipelle
Control group	No procedure	Placebo procedure	Placebo procedure
Intervention timing	Between day of the cycle prior to IVF, until day 3 of the IVF cycle	Between days 1–12 of the first study cycle	Between days 1–12 of the first study cycle
Blinding	Open label	Single-blind (participants are blind)	Single-blind (participants are blind)
Number of study cycles/opportunities to conceive	One	Three	Three
Study diary	No	Yes	Yes

### Study procedures

A gynaecologist or trainee gynaecologist with experience in performing endometrial biopsies will undertake the endometrial biopsy and placebo procedures. Participants may be advised to attend with a full bladder and to take paracetamol prior to the procedure to minimise any discomfort.

